### Sample Size Calculation

A total of 2920 RA patients were seen at the site of recruitment between April 30, 2013, and May 1, 2014. Of these patients, 1980 were prescribed at least one DMARD between April 30, 2013, and May 1, 2014, and approximately 60.00% (1188/1980) had moderate-to-high disease activity. From the 2013 Pew Internet Tracking Survey, we estimate that 50% of these patients (594/1980) own mobile phones [41]. Of these 594 individuals, we expect 80.1% (476/594) to meet the remainder of the inclusion criteria (≥18 years old, English speaking), and 40.0% (190/476) to agree to participate.

On the basis of previous studies examining differences in patient satisfaction, the expected difference between groups is 9.4 (SD 18.4) in TSQM scores [42,43]. No data exist regarding the expected difference in CDAI scores for this intervention. However, the minimal clinically important difference in CDAI scores is 12 [44,45]. On the basis of attrition rates from previous studies, we expect ≥61% (122/190, 64.2%) subjects to complete the study. Given a sample size of 122 subjects and an alpha level of .05, we will be able to reject the null hypothesis that the population means of the experimental and control groups are equal with probability (power) 0.80 to 0.99.

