#### Randomization (Disease Activity Levels)

Participants will be randomized 1:1 using a publicly available Web-based randomization tool. Randomization will occur within categories stratified by disease activity, assessed by the CDAI: remission (≤2.8), low (>2.8-10), moderate (>10-22), and high (>22) [17].

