### Outcome Measures

To assess patient satisfaction, the primary outcomes will be scores on the TSQM and PEPPI questionnaire at 6 months [21,22]. To determine the effect of the mobile app on RA disease activity, the primary outcome will be CDAI at 6 months [17].

The TSQM is a validated questionnaire that assesses medication satisfaction [21]. The different components of medication satisfaction are the following: side effects, effectiveness, convenience, and overall satisfaction. There are 14 questions, scored on a 5- or 7-point Likert scale. Responses to each question are assigned a score between 0 and 100, with 0 being extremely dissatisfied to 100 being extremely satisfied. The TSQM was initially validated in a national study of chronic disease, including patients with arthritis, asthma, depression, hyperlipidemia, hypertension, migraine, and psoriasis. It was subsequently validated in separate populations of patients with multiple sclerosis, cystic fibrosis, and coronary disease [30-32]. In one study, ceiling and floor effects were observed in the side effects domain [32]. Of note, if these effects are a problem, a separate score (TSQM-9) can be calculated, removing the 5 items in the side effects domain. This abbreviated score was shown to have good construct and convergent validity, along with high internal consistency and good test-retest reliability [33]. In a study of individuals with chronic illnesses including 25.6% (44/172) RA patients, representative scores on the TSQM were 77.1 (SD 25.2) for side effects, 61.6 (SD 24.16) for effectiveness, 66.1 (SD 17.1) for convenience, and 68.8 (SD 20.6) for overall satisfaction [34]. Although no studies have specifically examined the responsiveness of the TSQM in RA, a study of osteoarthritis patients revealed that perceptions of convenience, effectiveness, and overall satisfaction increased with treatment with a nonsteroidal anti-inflammatory drug [35]. The TSQM has also been used in clinical trials of RA patients to compare patient satisfaction with the effects of different DMARDs [36].

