The PEPPI is a validated questionnaire that assesses self-efficacy in the patient-physician interaction [22]. It consists of 10 questions, scored on 5-point Likert scales, reflecting very confident to not confident at all. In multiple studies of elderly individuals and patients with osteoarthritis, the PEPPI showed construct, convergent, discriminant, and structural validity [22,37,38]. Although a ceiling effect was noted in the PEPPI 10-item scale, no ceiling effects were noted using the abbreviated 5-item scale, and no floor effects were noted for either scale [37-39]. Of note, the PEPPI was recently used in a 12-month RCT of an eHealth interactive self-assessment website (Sanoia) in RA [40]. The 320 participants in this study were similar in age, sex, and disease duration to the population we are recruiting. The mean baseline PEPPI score was 39.2 (SD 7.8). Participants randomized to receive the active intervention had small increases in their PEPPI score (mean 0.6, SD 5.2), whereas participants randomized to the control arm had concurrent decreases in their PEPPI score (mean ‒-0.91, SD 6.08). Although the magnitude of change was small, the difference between the 2 groups was statistically significant (*P*=.01), indicating that this instrument is able to detect differences between an active self-monitoring intervention and control.

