### Statistical Analysis

The primary analysis will be a completer analysis. Summary statistics (eg, frequencies, means, and medians) of the baseline variables will be calculated to assess the effectiveness of randomization. Treatment effects (mean differences in outcomes between the 2 groups at 3 and 6 months) will be estimated with mixed models. This model includes the interaction of treatment and time and allows adjustment for baseline scores. For each outcome measure, we will also adjust for age, sex, race, disease duration, and any variables that are statistically different from each other in unadjusted analyses (*P*<.10). A 2-tailed *P* value of .05 will be considered significant. All analyses will be conducted by a blinded statistician using SAS 9.3 (SAS Institute).

On the basis of previous studies performed by this research group within this population, we do not expect a large amount of missing data in the primary outcome measures and covariates. These data are obtained during in-person study visits. A research assistant is present during all study visits and checks forms for completion. When necessary, multiple imputation by chained equations will be used to impute missing variables.

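### The power range of 0.80 to 0.99 names no outcome and has no PEPPI input; at the only PEPPI effect the protocol cites, power with 122 completers is about 0.31 to 0.35

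*Protocol article*

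**What the plan says.** The Outcome Measures section (Protocol article) makes PEPPI primary: "To assess patient satisfaction, the primary outcomes will be scores on the TSQM and PEPPI questionnaire at 6 months". CDAI at 6 months is added as the primary outcome for disease activity.

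The Sample Size Calculation section gives an expected TSQM difference of 9.4 (SD 18.4) and a minimal clinically important CDAI difference of 12 with no SD. It gives nothing for PEPPI. On attrition it states: "we expect ≥61% (122/190, 64.2%) subjects to complete the study". It then gives one power statement. It begins "Given a sample size of 122 subjects and an alpha level of .05" and ends by saying that the trial can reject the hypothesis that the "population means of the experimental and control groups are equal with probability (power) 0.80 to 0.99". No outcome is named.

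The only PEPPI effect data are in Outcome Measures, from a 12-month trial of a self-assessment website in 320 RA patients described as similar to those being recruited: "Participants randomized to receive the active intervention had small increases in their PEPPI score (mean 0.6, SD 5.2"). The control arm fell by 0.91 (SD 6.08), the P value was .01, and the baseline SD was 7.8. The protocol uses these figures to argue that the instrument can separate a self-monitoring intervention from control.

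**The concern.** With three primary outcomes and one power range that names none of them, a reader will take the range to cover all three. PEPPI has no input in that section, and the PEPPI effect quoted a few paragraphs earlier is small relative to its SD (1.51/5.66 = 0.27 SD). The TSQM effect behind the 0.80 is 0.51 SD. The trial cited as evidence that PEPPI can detect a difference had 320 participants, whereas this one expects 122 completers.

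What is at stake is how a non-significant PEPPI result will be read. Set beside a stated power of at least 0.80, it would look more informative than it is if the true effect is near the cited one.

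**Working it through.** **Inputs.** Two-sided 0.05 (Statistical Analysis: "A 2-tailed *P* value of .05 will be considered significant"); 122 completers; 1:1 allocation, hence 61 per arm; effects and SDs as listed above.

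**Formula.** Noncentrality = difference / (SD × √(2/61)), with √(2/61) = 0.1811. Power comes from the noncentral t with 120 df. The normal approximation is Φ(noncentrality − 1.960).

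**Step 1: reproduce the 0.80 (TSQM).** 9.4 / (18.4 × 0.1811) = 2.82. Power is 0.799 (t) or 0.805 (normal). The normal-approximation sample size is 61 per arm, that is 122. The lower bound is the TSQM figure.

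**Step 2: locate the 0.99 (CDAI).** The difference is 12 and no SD is given, so the SD is an assumption. Normal-approximation power at 61 per arm:

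| Assumed CDAI SD | Power |
|---|---|
| 12 | >0.999 |
| 15 | 0.993 |
| 15.5 | about 0.99 |
| 18 | 0.957 |
| 20 | 0.912 |

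The upper bound is plausible for CDAI but cannot be verified.

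**Step 3: PEPPI at the cited effect.** Difference = 0.6 − (−0.91) = 1.51.

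Three SD choices are possible:
- Change score: √((5.2² + 6.08²)/2) = √32.00 = 5.66.
- Baseline-adjusted: assume follow-up SD equals the baseline SD of 7.8. Then r = 1 − 32.00/(2 × 7.8²) = 0.737, and the residual SD = 7.8 × √(1 − 0.737²) = 5.27.
- Raw score, no adjustment: 7.8.

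The difference detectable at 0.80 is (1.960 + 0.842) × SD × 0.1811 = 0.507 × SD. The number per arm for 0.80 at 1.51 points is 2 × (2.802 × SD/1.51)².

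| SD used | Power, 61 per arm | Power if all 190 complete | Per arm for 0.80 | Detectable at 0.80 |
|---|---|---|---|---|
| 5.66 (change) | 0.31 | 0.45 | 221 | 2.9 |
| 5.27 (adjusted) | 0.35 | 0.50 | 192 | 2.7 |
| 7.8 (raw) | 0.19 | 0.26 | about 420 | 4.0 |

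Using either arm's change SD alone moves the 0.31 only to 0.36 (SD 5.2) or 0.27 (SD 6.08). To reach 0.80 for 1.51 points with 61 per arm, the SD would have to be about 1.51/0.507 = 3.0, well below any SD the protocol reports for PEPPI.

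**Step 4: are the cited figures coherent?** Assuming 160 per arm, SE = 5.66 × √(2/160) = 0.632, z = 2.39 and P = 0.017, close to the reported .01. The 1.51 and its SDs are therefore not a transcription artefact.

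**The case against.** The strongest reply is that the protocol never claims a PEPPI power. The paragraph has two inputs, TSQM and CDAI, and a range with two ends. Step 1 matches the lower end to TSQM, and step 2 shows the upper end is plausible for CDAI. On that reading PEPPI was simply left out, and no PEPPI calculation exists to be wrong. This stands as an account of where the range came from. A reader might infer that the authors computed PEPPI power and got it wrong, or that the 0.80 itself is an error. The documents support neither. What remains is that the sentence is unqualified while PEPPI is a primary outcome.

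The second reply is that 1.51 points is not a design assumption here. It comes from a 12-month trial of a website. This trial ends at 6 months and tests an app with alerts handled by a population manager, and both arms have such a manager. The true effect could be larger or smaller. That also stands: the power of 0.31 is conditional on a borrowed effect. A reader might go further and conclude that the trial will miss a real PEPPI benefit about two times in three. That holds only if the true difference is near 1.5 points, which the protocol does not assert. Equally, it gives no basis for expecting the 2.7 to 2.9 points needed.

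Third, an article may leave a per-outcome breakdown to a fuller document. That excuses a missing table. It does not excuse a printed range that other figures in the same article do not bear out for one of the primary outcomes.

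**Conclusion.** The point holds as a defect in the power statement, not in the TSQM arithmetic. The range of 0.80 to 0.99 is presented without limit, has no PEPPI input, and is not met for PEPPI at the only effect the protocol cites. Power there is about 0.31 on change scores and about 0.35 with baseline adjustment, which is nearer the planned mixed model. It is 0.19 with the raw SD. Even full retention of 190 gives no more than about 0.50.

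These figures rest on 61 completers per arm, two-sided 0.05, the cited effect carrying over from 12 to 6 months and to a different intervention, and, for 0.35 only, equal baseline and follow-up SDs (r about 0.74). The 0.99 remains unverifiable without a CDAI SD.

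It does not follow that PEPPI should cease to be primary. The trial is registered and recruitment began in November 2016, so demoting it now would be a substantive change to a running trial rather than a wording correction, and low power at a borrowed effect does not by itself require it.

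**What to change.** Replace the single range in Sample Size Calculation with one statement per primary outcome:

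- **TSQM:** 122 completers (61 per arm) give power of about 0.80 for a difference of 9.4, SD 18.4.
- **CDAI:** tie the upper figure to this outcome and state the SD assumed. A figure of 0.99 for a difference of 12 implies an SD of about 15.5; if another SD was used, give it and the matching power.
- **PEPPI:** 122 completers give about 0.31 to 0.35 power for a 1.5-point difference, and 0.80 only for about 2.7 to 2.9 points (about 4.0 with the raw SD of 7.8). Name the SD and, for the adjusted figure, the assumed correlation. Say that the 1.5 points come from a 12-month trial of a different intervention.

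Keep PEPPI as a primary outcome with these figures disclosed. Sample size, conduct and analysis are unchanged. The cost is a less favourable stated power for one primary outcome.

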### Fidelity of the Intervention

In addition to the assessments of satisfaction and efficacy described above, we will also assess the fidelity of the intervention. Systems are in place to monitor survey completion rates, and an alert is issued to the population manager if participants have not answered a survey in the past 7 days. Information is also obtained on the exit survey to determine whether participants were able to download the app.

## Results

Recruitment is currently underway. We started patient recruitment in November 2016 and will continue until the recruitment goal of 190 participants has been achieved. Findings on the study’s primary outcomes are expected to be finalized by September 2019. Thus far, user feedback from both RA patients and HCPs has been positive. RA patients have particularly enjoyed the ability to track their disease activity and symptoms and to share these results, using the app’s graphic interface, with their family members. HCPs have appreciated receiving information about their patients between regularly scheduled clinic visits.

## Discussion

### Summary and Strengths

The findings from this study will represent the first randomized trial to test the effects of a combined mobile app and the population management system on a patient population with RA. Although several mobile apps exist to monitor symptoms of chronic disease, none have incorporated the use of a population management system for the management of disease activity in RA. This manuscript was written meeting the checklist to report health interventions using mobile phones [46].

In a systematic review of mobile apps to assist RA patients in disease management, Grainger et al reported that high-quality apps, including monitoring tools that assess disease activity using validated instruments, are lacking [47]. They also noted the importance of delivering the tools via a user-friendly interface. Our medical team collaborated with the local app developer, as well as other experienced developers, to address these 2 issues. First, we worked with the local app developer to incorporate a validated measure of self-reported RA, the RADAI-5, and PROMIS assessments of pain interference, physical function, fatigue, depression, and sleep disturbance. Second, we met experienced app developers to get advice regarding the user interface during the development stages. The developers provided valuable feedback, including suggestions to create large menu buttons at the bottom of the screen rather than to rely on a list of menu options as a dropdown box along the side. As a result, we were able to develop a mobile app that incorporates useful information for physicians, while also being easy for patients to enter and visualize data.

We foresee tangible benefits to both patients and HCPs. For patients, an app can be beneficial by providing tools to easily track and record their disease trajectories. If successful, this system may spark greater patient engagement in self-management of RA. People with chronic diseases have been more engaged in using mobile apps in managing their diseases than people managing other aspects of their health [48]. For HCPs, an app and a population management system may be beneficial by providing a more complete picture of their patients, beyond the snapshots they currently see during scheduled clinic visits. We specifically created the combined app and population management system so that it does not create a large amount of work for busy HCPs. Instead, we maximize the use of other trained staff members (eg, population managers) and only involve HCPs when clinically significant events are identified by flare alerts. This increased reservoir of information may then serve as a catalyst for more effective patient-HCP communication. A formal cost assessment was not performed as this is a research study designed to assess feasibility and efficacy, and the costs involved in this endeavor will likely differ from actual implementation in the clinic setting.

### Barriers and Limitations

Many barriers have occurred during app development and study implementation. Specifically, beta-testing took more time than we planned, and, as a result of beta-testing, additional revisions were required. After the app was developed, regular maintenance and updates were required. These included testing and updates for new releases of the iOS and Android operating systems and cross-device and browser testing for new device and browser versions. In addition, implementation of the study was disrupted for a period of 2-6 days when surveys were not sent to participants due to disruptions in server access. These difficulties highlight the importance of ensuring that timelines include appropriate consideration for beta-testing, and budgets include appropriate resources for support and maintenance activities.

A major limitation is that this system is not integrated with the existing electronic medical record (EMR). Although we originally sought to integrate this system, multiple factors intervened. Specifically, the hospital system changed EMRs during the planning phase of this study. Thus, the institution’s information technology priorities were focused on the clinical implementation of the new EMR, not on research endeavors. In addition, as a result of the transition in EMRs, HCPs were required to complete multiple training sessions and change their workflow to accommodate the new EMR. As a result, additional meetings with HCPs to discuss the best strategies for integration into the EMR were not possible at this time. The ability to translate this pilot study to a large-scale clinical implementation will depend on integration with the EMR. Although technically possible, integration with the EMR will require much negotiation with hospital administration and HCP groups, as well as an appropriate budget to fund the processes to support this integration.

In addition, we expect a fair amount of missing data from the app due to varying engagement from participants. However, our primary objective is not to use these data in statistical analyses; rather, our intention is that these data be useful to patients in monitoring and understanding their disease. Even if patients do not enter 50% of the data, they will still, on average, have at least 1 data point for disease activity per week and at least 1 data point for each of the other symptoms every 2 weeks. These data, in themselves, can be helpful and are more than is normally obtained without the aid of a disease activity and/or symptom tracker. We will also analyze the completion rates of daily surveys as proxies for patient engagement and overall feasibility.

Other limitations include the following: (1) the possibility of a ceiling effect if most participants have low disease activity and score well on the primary outcome measures, even at baseline; (2) the study being available only to English speakers, as not all of the surveys have been validated in other languages; and (3) limited generalizability, as we are only enrolling individuals who own a mobile device and, therefore, are likely receptive to mobile technology. In a study of 9183 participants in the Arthritis Internet Registry, older age and lower income were significantly associated with lower rates of mobile phone ownership [20]. However, recent studies suggest that mobile phone ownership is growing at a rapid rate, even among individuals over 50 years. On the basis of a 2016 report by the Pew Research Center, 74% of individuals between 50 and 64 years of age now own a mobile phone, a number which is up from approximately 50% in 2013 [49,50]. Similarly, mobile phone ownership in low-income households (<US $30,000/year) now exceeds 50% and continues to rise [51].

### Conclusions

The successful implementation of a mobile device and population management system may help integrate patient-reported data into the workflow of a busy clinical practice. We expect this model to be easily adaptable to other rheumatic conditions, as well as nonrheumatic chronic illnesses. The PROMIS questionnaires used in this study were specifically developed to be relevant across different conditions for the assessment of symptoms and functions, and we anticipate that a mobile app combined with a population management system will have broad applicability in helping patients better understand their disease, improving patient-HCP communication and, ultimately, improving disease management and overall satisfaction in their care.

## Appendix

Multimedia Appendix 1 Physician exit form.

Multimedia Appendix 2 Physician study visit follow-up questions.

## Abbreviations

CDAI: Clinical Disease Activity Index
DMARD: disease-modifying antirheumatic drug
EMR: electronic medical record
HCP: health care provider
PEPPI: Perceived Efficacy in Patient-Physician Interactions
PROMIS: Patient-Reported Outcomes Measurement Information System
RA: rheumatoid arthritis
RADAI-5: Rheumatoid Arthritis Disease Activity Index-5
RCT: randomized controlled trial
TSQM: Treatment Satisfaction Questionnaire for Medication
